## Abstract

**Background:**

Recent findings on the benefits of glibenclamide as a neuroprotective drug have started a new era for prospective studies on sulfonylureas. The effect of glibenclamide blocking the Sur1-Trpm4 channel was examined in models of subarachnoid hemorrhage and stroke, with findings of significantly reduced tight-junction abnormalities, resulting in less edema formation and considerably reduced transsynaptic apoptosis of hippocampal neurons and significantly ameliorated impairments in spatial learning. Based on these data, we plan a clinical trial to establish evidence of glibenclamide as an adjunct treatment in aneurysmal subarachnoid hemorrhage.

**Methods:**

An estimated 80 patients meeting the inclusion criteria of radiological confirmatory evidence of an aneurysmal subarachnoid hemorrhage, age 18–70 years, and presentation of less than 96 h from the ictus will be allocated randomly into two groups, one receiving 5 mg daily oral intake of glibenclamide for 21 days and another control group receiving a placebo. The study’s primary outcome is the modified Rankin scale (mRS) after 6 months, as favorable (mRS 0–2) or unfavorable (mRS 3–6). The secondary outcomes will be late cognitive status, assessed after 6 months by psychological tests (the Short Form Health Survey Questionnaire and the Montreal Cognitive Assessment), as well as death at 6 months, delayed cerebral ischemia and occurrence of serious adverse events due to study medication.

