### Sample size

We estimated a sample size of 80 randomized patients to give 90% power at the 5% significance level (two-sided) to detect a treatment effect equivalent to an absolute increase of 7% in the proportion of patients with a favorable outcome (30-day mortality rate after subarachnoid hemorrhage approaches 40% and 25% of survivors present some degree of neurological morbidity [24]). This calculation was based on an ordinal analysis of the 6-month mRS (the primary outcome), assuming that the treatment effect follows a proportional odds model.

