## Statistical analysis

The analysis of outcome measures will be on the intention-to-treat population, including those who died during the first 21 days. Results will be presented as an adjusted common odds ratio (OR) with a corresponding 95% confidence interval (CI), with values of the common OR of less than 1 indicating a treatment effect in favor of glibenclamide, with values of *p* < 0.05 considered statistically significant. Additionally, an analysis using logistic regression will be performed with the same covariates as specified above, adopting the conventional dichotomy of favorable mRS (0–2) versus unfavorable mRS (3–6). We will perform all analyses using the Mann Whitney *U* test, χ^2^ test or two-sample *t* tests as appropriate.

All statistical analysis will be performed with the SPSS Statistics for Windows software (IBM Corp., v. 24.0, Armonk, NY, USA). The analysis will also be blind for group allocations.

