### Expected outcomes

The primary outcomes will be the distribution of the mRS score assessed after 6 months of the end of the intervention, as favorable (mRS 0–2) and unfavorable (mRS 3–6). Secondary outcomes will be the cognitive assessment and quality of life as measured by the neuropsychological tests, as well as death, delayed ischemic deficits and the occurrence of serious adverse events attributable to medication. These secondary outcomes were preselected to provide supportive evidence related to the primary outcome.

The definition of delayed cerebral ischemia, as elaborated on by Vergouwen et al. [25], is taken as the occurrence of focal neurological impairment (such as hemiparesis, aphasia, apraxia, hemianopia, or neglect), or a decrease of at least 2 points on the Glasgow Coma Scale (either on the total score or on one of its individual components (eye, motor on either side, verbal)). This should last for at least 1 h, is not apparent immediately after aneurysm occlusion, and cannot be attributed to other causes by means of clinical assessment, computed tomography or magnetic resonance imaging of the brain, and appropriate laboratory studies. We will report any serious adverse events and those that were deemed to be related to the trial medication.

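### The outcome definitions make the 6-month mRS dichotomous while the sample size and lead analysis make it ordinal, so either result could be presented as the prespecified primary

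*Protocol article*

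**What the plan says.** Four places in the protocol article bear on the primary endpoint.

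- **Abstract, Methods:** "primary outcome is the modified Rankin scale (mRS) after 6 months, as favorable" for scores of 0 to 2, set against the opposite class for 3 to 6. This is a binary endpoint.
- **Expected outcomes:** "The primary outcomes will be the distribution of the mRS score assessed after 6 months of the end of the intervention". The sentence speaks of a distribution but then describes two categories, divided at the same point.
- **Sample size:** "This calculation was based on an ordinal analysis of the 6-month mRS (the primary outcome), assuming that the treatment effect follows a proportional odds model". The target effect in the same paragraph is nevertheless a 7-point rise in the favorable proportion.
- **Statistical analysis:** "Results will be presented as an adjusted common odds ratio (OR) with a corresponding 95% confidence interval (CI", with the 0.05 threshold in that same sentence. Then: "Additionally, an analysis using logistic regression will be performed", using the 0–2 versus 3–6 split and covariates said to have been specified earlier, although the article lists none. The paragraph ends by assigning all analyses to Mann-Whitney, chi-square or two-sample t tests.

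Nowhere is one analysis labelled primary, and no split or adjustment of alpha is given.

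**The concern.** A reader of the Abstract or Expected outcomes takes the comparison of favorable proportions as the primary result. A reader of Sample size takes the ordinal comparison. The two tests answer related but different questions and need not agree. Once data are available, whichever is significant could be reported as the prespecified primary result, with a supporting sentence from the article. That freedom raises the chance of a false positive claim above 5%. The closing sentence on simple tests adds a third prescription, which fits neither the adjusted ordinal model nor the adjusted logistic model.

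Timing matters. Trial status reports 36 patients recruited, most still in follow-up. Safety considerations plans an interim analysis once 40 have completed follow-up, and Project duration and management has one author see allocations at the half-way point. A choice made before then is credible; one made afterwards is less so.

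**Working it through.** **1. The passages side by side**

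| Section | Form of the primary endpoint |
|---|---|
| Abstract, Methods | Dichotomous |
| Expected outcomes | Called a distribution, described as dichotomous |
| Sample size | Ordinal, proportional odds |
| Statistical analysis | Common odds ratio first, dichotomous model as an addition, then simple tests for all analyses |

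The two sections that define the outcome conflict with the two that specify its analysis.

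**2. Does the plan's figure of 80 settle which was meant?**

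No control rate is stated. The mortality and morbidity figures in Sample size suggest 0.60 × 0.75 = 45% favorable (an assumption), so 52% under treatment. The odds ratio in magnitude is (0.52/0.48)/(0.45/0.55) = 1.324, with log 0.281.

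- *Ordinal (Whitehead):* N = 12(z₀.₉₇₅ + z₀.₉₀)² / [(log OR)²(1 − Σp̄³)]. With seven equal categories this is 12 × 10.51 / (0.0788 × 0.980) ≈ 1,634 in total. With an illustrative mRS of 45% favorable and 40% dead it is 1,708, and with only three categories 1,921.
- *Dichotomous (two proportions):* 1,070 per arm, 2,140 in total.

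Neither reading reproduces 80, so the figure cannot identify the primary analysis.

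**3. Type I error if either test may count**

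Inputs: 40 per arm (80 randomized 1:1, no dropout), two-sided 5%, and the same mRS distribution in both arms. The article gives no distribution, so four were assumed. There were 200,000 simulated trials for each, without covariates.

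- *Ordinal:* tie-corrected Mann-Whitney, the score test of the proportional-odds model. z = (W − n(N+1)/2)/√V, where V = (n²/12)[(N+1) − Σ(t³−t)/(N(N−1))], n = 40, N = 80.
- *Dichotomous:* Pearson chi-square on 0–2 versus 3–6. z = (p₁ − p₀)/√(2p̄(1−p̄)/n).

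| Assumed mRS 0 to 6 (%) | Ordinal | Dichotomous | Either | Correlation of z | Tests disagree, given at least one significant |
|---|---|---|---|---|---|
| 15, 15, 15, 5, 5, 5, 40 | 4.95% | 5.47% | 7.34% | 0.89 | 58% |
| seven equal | 5.03% | 5.43% | 7.67% | 0.86 | 64% |
| 10, 20, 15, 6, 6, 3, 40 | 4.94% | 5.49% | 7.36% | 0.89 | 58% |
| 10, 20, 25, 15, 10, 5, 15 | 4.94% | 5.49% | 7.61% | 0.87 | 63% |

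Independent tests would give 1 − 0.95² = 9.75%. The strong correlation keeps the rate near 7.5%.

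**4. Power at the plan's own effect**

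With a 7-point rise added to each of the four distributions, 80 patients give simulated power of 10.6–11.0% for the ordinal test and 10.1–10.6% for the dichotomous one.

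**The case against.** The strongest reply is that the article does rank the two analyses. Sample size attaches the ordinal method to the primary outcome. Statistical analysis puts the common odds ratio first and introduces the logistic model as an addition. That stands: the analysis sections lean ordinal. It does not remove the conflict, because both outcome definitions remain dichotomous.

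A second reply is that a full protocol or SAP may fix the decision rule. It may, and the absence of a formal rule is not the complaint here. But the article states two incompatible definitions, so at least one published statement would still need correction.

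Two stronger readings are tempting and are not supported:

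- *A reader might infer that both tests are declared at 0.05 and that either suffices.* The text does not say so. The threshold stands in the common-odds-ratio sentence; the logistic sentence gives neither a threshold nor a success rule. The either-test rate describes what the ambiguity permits, not a rule that the plan adopts.
- *A reader might infer that taking the dichotomy as primary would sacrifice important power.* A visible gap appears only at much larger effects than the plan states. At its own 7 points the two tests are practically equal, at about 10–11%.

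Part of the excess over 5% is also not due to choosing between tests: the uncorrected chi-square alone runs at about 5.5% with 40 per arm.

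**Conclusion.** The contradiction holds and can be read directly from the article. The definitions say dichotomous, the sample-size basis and lead analysis say ordinal, and the closing sentence on simple tests fits neither adjusted model. If either test could be counted, type I error would be about 7.5% (7.3–7.7% over the assumed distributions). That is 2.4–2.7 points above the ordinal test alone and 1.9–2.2 points above the dichotomous test alone. The harm is therefore real but moderate. Among null trials with at least one significant test, the two disagree in about 58–64%, so the choice can change the conclusion.

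These figures assume the mRS distributions shown, complete follow-up of 40 per arm and unadjusted tests; adjusted models may differ somewhat. No loss of power is claimed. That 80 patients cannot deliver 90% power for a 7-point effect under either reading is a separate problem, which this point neither depends on nor resolves.

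**What to change.** Before the interim analysis, and before anyone choosing the analysis sees outcomes by arm:

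1. Put one statement in the Abstract, Sample size, Statistical analysis and Expected outcomes: the primary outcome is the full seven-level mRS at 6 months, analysed by a proportional-odds model (common odds ratio), and this analysis alone decides the primary conclusion.
2. Label the 0–2 versus 3–6 logistic regression as secondary.
3. Limit the Mann-Whitney, chi-square and t-test sentence to the other outcomes.
4. Name the adjustment covariates from baseline data already collected, such as WFNS grade, or drop the word adjusted.

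The ordinal choice matches the plan's own sample-size basis and order of analyses. A consistently dichotomous primary would also remove the contradiction, but would require rewriting those two sections.

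The cost is a wording amendment and a check that the registry entry agrees. No extra patients or data are needed.

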**Discussion:**

There is a growing interest in the scientific community regarding glibenclamide in brain edema and traumatic brain injury, but with very little of this interest targeting spontaneous brain hemorrhage, especially aneurism rupture. Positive outcomes are expected for the treatment patients, especially in language and memory preservation, as has been shown in experimental models.

**Trial registration:**

ClinicalTrials.gov, NCT03569540. Retrospectively registered on 26 June 2018.

**Electronic supplementary material:**

The online version of this article (10.1186/s13063-019-3517-y) contains supplementary material, which is available to authorized users.

## Background

Subarachnoid hemorrhage from a ruptured intracranial aneurysm is a common type of stroke and is of substantial clinical and socioeconomic relevance, affecting about 600,000 patients worldwide every year. Subarachnoid hemorrhage accounts for a great deal of death and disability, particularly because it affects a younger age group than other stroke subtypes. Combined morbidity and mortality reach up to 50%, with 30% of survivors remaining dependent. Additionally, 20–30% of patients in hospital admission, initially with a good clinical grade, can have poor outcomes. These high rates of morbidity and mortality are mainly related to the extent of bleeding and other complications, including cerebral vasospasm. Clinical treatment has been largely ineffective at improving the outcome. A selective calcium channel blocker (nimodipine) remains the only evidence-based option in the management of subarachnoid hemorrhage, although with limited benefits. Conversely, delayed ischemic deficits represent the main source of neurological disability after cerebral aneurysm rupture, and prevention of cerebral arterial vasospasm constitutes a key target for new pharmacological treatments. Other options include statins and magnesium sulfate. However, recent trials have been unable to demonstrate any clinical benefits.

There is experimental and clinical evidence that sulfonylureas may be beneficial for patients with acute ischemic stroke. The pleiotropic neuroprotective effects of glibenclamide have been well substantiated over the past decade in clinically relevant models of human disease. Glibenclamide protects the microvascular endothelium to reduce the formation of edema and secondary hemorrhage, inhibits neuronal cell death, and exerts potent anti-inflammatory effects and promotes neurogenesis. Retrospective studies of patients with diabetes, as well as a recent Phase IIa pilot study in nondiabetic individuals, suggest a highly promising translational potential for therapeutic intervention with glibenclamide in ischemic stroke.

### Background information

Glibenclamide is a member of the sulfonylurea class of drugs and has been in clinical use as an oral hypoglycemic agent since the 1960s. Sulfonylurea drugs all work via a similar mechanism which is inhibition of the sulfonylurea receptor 1 (Sur1). Glibenclamide has received renewed attention due to its pleiotropic protective effects in acute central nervous system (CNS) injury [1–17]. In the CNS, glibenclamide exerts its effects primarily via inhibition of the recently characterized Sur1-Trpm4 channel (formerly, the Sur1-regulated nonselective cation (NC_Ca-ATP_) channel). Inhibition of Sur1 with glibenclamide has found to be an effective treatment in experimental models of various CNS pathologies, including ischemic and hemorrhagic stroke and subarachnoid hemorrhage [17–19].

### Experimental data

Experimentally, glibenclamide significantly reduced the mortality rate to 5% in models of ischemic stroke, whereas the vehicle-treated group had 67% mortality at 24 h. Compared to the decompressive craniectomy (DC) group, glibenclamide-treated rats exhibited less brain swelling at 24 h and improved neurological outcome that persisted for the 2 weeks of observation. Both DC and glibenclamide eliminated mortality, but neurological function during the next 2 weeks was significantly better with glibenclamide compared with DC [17].

### Clinical studies in ischemic stroke

Retrospective studies of patients with diabetes mellitus type II suffering from ischemic stroke suggest that being on a sulfonylurea drug and staying on it during hospitalization for stroke improves outcome and reduces the incidence of symptomatic hemorrhagic transformation and mortality [16, 17]. Recently, Phase II clinical trials have begun to evaluate an intravenous formulation of glibenclamide in patients with traumatic brain injury [20] and stroke [21–23]. The neuroprotective properties observed in the laboratory and in retrospective human studies have led to the initiation of prospective clinical trials in ischemic stroke and traumatic brain injury. These prospective trials are evaluating an injectable formulation of glibenclamide (RP-1127; Remedy Pharmaceuticals, Inc., New York, NY, USA). Recently, a two-center, prospective, open label, Phase IIa pilot study of RP-1127 was completed (ClinicalTrials.gov identifier NCT01268683) [23]. This clinical trial tested the effect of RP-1127 in 10 patients with a severe anterior circulation ischemic stroke at high risk for malignant cerebral edema. The incidence of malignant edema was 20%, compared with 88% in a prospective observational study of patients. Moreover, 8/10 patients did not require osmotherapy, intubation, or DC.

### Glibenclamide and experimental subarachnoid hemorrhage

The effect of glibenclamide was examined in a model of subarachnoid hemorrhage [19]. Twenty-four hours after injury, subarachnoid hemorrhage caused a large increase in blood–brain barrier permeability and disrupted the normal junctional localization of the tight-junction protein zona occludens (ZO-1). Glibenclamide significantly reduced ZO-1 abnormalities, resulting in less edema formation. In addition, subarachnoid hemorrhage led to large increases in several markers of inflammation, including tumor necrosis factor α and nuclear factor-κB, and markers of cell injury or cell death, including immunoglobulin G endocytosis and cleavage of caspase-3. Glibenclamide significantly reduced these effects as well. Glibenclamide considerably reduced transsynaptic apoptosis of hippocampal neurons, reduced venous congestion and significantly ameliorated impairments in spatial learning [16, 18].

### Clinical use of glibenclamide in subarachnoid hemorrhage

Glibenclamide has not been tested in the clinical treatment of subarachnoid hemorrhage thus far. Inflammation and delayed ischemic deficits account for a great deal of postaneurysmal rupture complications. The biological properties of glibenclamide may counterbalance inflammatory and ischemic consequences of subarachnoid hemorrhage, leading to better clinical outcomes. We believe that a clinical trial testing the effects of glibenclamide on the outcomes of patients with subarachnoid hemorrhage is currently fully supportable.

## Study goals and objectives

Thus far, there is no clinical study to evaluate the potential benefits of glibenclamide after aneurysmal subarachnoid hemorrhage. The time delay of 3 to 10 days until cerebral vasospasm develops after aneurysm rupture offers the unique opportunity to intervene before ischemia occurs. In this application, we outline a proposal to investigate the impact of the use of glibenclamide on the outcome of patients with aneurysmal subarachnoid hemorrhage. This information has major relevance, since subarachnoid hemorrhage is a prevalent condition and is a major cause of neurological disability and death. The lack of effective pharmacological measure to improve outcome in this scenario may be fulfilled by glibenclamide, with a significant medical and socioeconomic impact.

### Primary objective

The primary objective is to evaluate the role of glibenclamide on the clinical outcome of patients with aneurysmal subarachnoid hemorrhage. A prospective, randomized, double-blind trial was designed to evaluate the following hypothesis: glibenclamide improves clinical outcome after aneurysmal subarachnoid hemorrhage as measured by the modified Rankin scale (mRS).

### Secondary objectives

The secondary objectives are to assess the safety and effect of glibenclamide on the mortality rate, quality of life and cognitive performance in patients with aneurysmal subarachnoid hemorrhage. A prospective, randomized, double-blind trial was designed to evaluate the following hypothesis: glibenclamide decreases mortality and improves quality of life and cognitive performance in patients with aneurysmal subarachnoid hemorrhage.

## Study design

Glibenclamide in aneurysmatic subarachnoid hemorrhage (GASH) is a double-blind, prospective, randomized clinical trial. Recruitment will take place between 2018 and 2019 (Table 1).

## Methodology

### Study setting

This study is set in the Hospital das Clínicas, University of São Paulo, Brazil. Patients will be recruited from neurological/neurosurgical intensive and emergency care units.

### Eligibility criteria

Inclusion criteria will be radiological confirmatory evidence of an aneurysmal subarachnoid hemorrhage (by digital subtraction angiography, computed tomography angiography, or magnetic resonance angiography), age 18–70 years, and presentation less than 96 h from ictus. Exclusion criteria will be patients taking glibenclamide therapy at presentation, pregnancy, no reasonable prospect of survival (Hunt and Hess V), known renal or hepatic impairment, patient not fully independent before bleed, strong suspicion of drug or alcohol misuse, patient taking warfarin-type drugs, and suspected additional life-threatening disease.

### Intervention

Patients will be randomly assigned (1:1) to receive either glibenclamide 5 mg or placebo. Coded bottles containing either 21 similar tablets of glibenclamide 5 mg or placebo will be assigned a number. Patients will start treatment as soon as possible within 96 h of the ictus, with a daily dose until the 21st day after the bleed. Trial medication consists of one tablet a day, given orally or via a nasogastric tube. Aneurysm treatment, either by microsurgery or embolization, will be performed as soon as possible, according to the standard of care for the recruiting center. Nimodipine 60 mg, every 4 h, will be started on admission and continued till the 21st day after the ictus in all patients as recommended. No patient will be discharged during the time of treatment for a proper side effect monitorization.

Patient demographics, medical history and relevant investigation results will be collected. The severity of the hemorrhage will be clinically assessed by the World Federation of Neurosurgical Societies grading scale and radiologically assessed using the modified Fischer scale. At 6 months of follow-up, patients will be analyzed with the mRS (a scale that measures degree of incapacity/dependence and mortality after neurological events) by a physician with no knowledge of treatment allocation. Neuropsychologists will also evaluate quality of life and cognitive performance using the Short-Form Health Survey Questionnaire (SF-36) and the Montreal Cognitive Assessment (MoCA) by their ten domains grade punctuation (0–100). We hypothesize that, compared with the control group, glibenclamide 5 mg will provide a better clinical outcome and additionally will decrease mortality and improve quality of life and cognitive performance after 6 months. Figure 1 shows the schedule of events.

**Table 1 Tab1:** Trial duration

	2017	2018	2019	2020
Planning	+			
Recruitment		+	+	
Follow-up		+	+	+
Statistical analysis				+
Writing and submission				+

